### Participant timeline {13}

The participants’ timeline begins with the screening for eligibility at ICU admission, obtainment of informed consent, enrolment, and randomized trial group allocation during the initial 24 h of stay. The calendar day in which group allocation takes place is considered trial “day zero” (D0).

The placement of the abdominal double-lumen catheter is intended to be performed as soon as possible after the allocation in the intervention group in order to optimize IAP and prevent and treat IAH. This procedure does not require special training beyond standard ultrasound-guided Seldinger technique.

Unforeseen catheter placement delay of more than 24 h after group allocation without clinical justification will lead to patient exclusion from the trial.

Protocol interventions and measurements will be maintained up to D7, after which post-trial care and follow-up will ensue until hospital discharge. This trial is expected to complete recruitment and follow-up of 70 patients in 36 months, until July 2025.

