#### Exclusion criteria

Exclusion criteria are defined by the following:Extreme age (≥ over 75 years old),Acute surgical condition or laparotomy in the preceding 4 weeks,Previous liver transplant,Hemorrhagic ascites (red blood cells count > 10,000/mL) [16],Extreme clinical severity (APACHE II ≥ 34),Any of the following conditions present 24 h after admission:aHemorrhagic shock with active uncontrolled bleeding,bRefractory shock (mean arterial pressure < 65 mmHg) despite multiple vasopressor support,Predictably short (< 72 h) ICU stay andTherapeutic futility determined by the medical staff.

Notes:These criteria are to be applied independently of any previous treatments of ascites, including recent LVP (i.e., in the emergency department before ICU admission), andExamples of “predictably short (< 72 h) ICU stay, precluding patient enrolment, may be, i.e., the reversal of clinical instability after initial therapy and adequate resuscitation in the ICU, such as < 6 h of vasopressor support; variceal bleeding controlled in the ICU without developing organ failure; or prompt reversal of oliguria/AKI.

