#### Control group—large-volume paracentesis

Ultrasound-guided (Ultrasound GE Vivid T8®) placement of an intra-abdominal catheter, 14 Gauge Optiva®, or similar, as indicated by the attending physician in accordance with international clinical guidelines [1, 12].Collection of ascitic fluid for laboratorial and microbiological analyses with every new paracentesis.Large-volume paracentesis will be performed as needed throught the ICU stay with a maximal duration of 8 h for each session.The volume of drained ascitis through LVP is determined by the attending physician, according to the usual clinical practice, without specified maximum volume limit.

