### Methods in analysis to handle protocol non-adherence and any statistical methods to handle missing data {20c}

Data will be analyzed according to intention-to-treat (ITT). Protocol adherence, with intervention initiation and completeness, will be reported. Missing data will not be imputated and will be described.

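### A late-catheter rule that only the CPP arm can trigger removes randomised patients, against the stated intention-to-treat analysis; separately, two shock criteria are timed later than allocation

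*Protocol article*

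**What the plan says.** All references are to the protocol article.

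- **Participant timeline {13}.** Allocation takes place within the first day: "randomized trial group allocation during the initial 24 h of stay". For the trial catheter, "The placement of the abdominal double-lumen catheter is intended to be performed as soon as possible after the allocation in the intervention group". The next paragraph adds that an unforeseen delay in placing it of more than 24 h "after group allocation without clinical justification will lead to patient exclusion from the trial".
- **Control group—large-volume paracentesis.** "Large-volume paracentesis will be performed as needed", on the attending physician's indication. No start time is set.
- **Methods in analysis to handle protocol non-adherence {20c}.** "Data will be analyzed according to intention-to-treat (ITT"). Initiation and completeness of the intervention are to be reported, and missing data are not to be imputed.
- **Who will be blinded {17a}.** Clinical staff, outcome assessors and analysts all know the allocation.
- **Exclusion criteria.** Two shock criteria come under the lead-in "Any of the following conditions present", followed by a time point of 24 h after admission.
- **Concealment mechanism {16b}.** The attending physician checks eligibility and settles enrolment before opening the envelope.

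**The concern.** Intention-to-treat keeps each randomised patient in the allocated arm whether or not the procedure was delivered on time. The timeline rule does the reverse: it takes a randomised patient out because the allocated procedure came late. It also works on one side only. A control patient who has no paracentesis for two days stays in the trial, while a CPP patient without a catheter over the same period can be removed.

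The trigger depends on whether a delay was clinically justified. The article does not define this, and the decision falls at least 24 h after allocation, when staff know both the arm and the early course. If the patients removed differ in prognosis from those kept, the two arms are no longer the groups that randomisation created. With 35 patients per arm, a few removals can matter.

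The shock criteria raise a different question. For anyone allocated before hour 24, status at hour 24 is not yet known when the envelope is opened, so the criteria cannot be applied as written at screening.

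**Working it through.** **Inputs from the protocol.** Sample size {14}: target difference 0.4 mg/dL; SDs 0.45 and 0.48; one-sided alpha 0.05; power 95%; 60 patients, raised to 70 for 15% non-adherence, attrition or violation; 1:1 allocation, hence 70/2 = 35 per arm.

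**1. The plan's own figure.** Pooled SD = √((0.45² + 0.48²)/2) = 0.465. A two-sample t-test with the noncentral t, one-sided 0.05 and 95% power, needs 60 in total, as stated. For the allowance, 60/0.85 = 70.6 and 60 × 1.15 = 69, so 70 is reasonable. The sample size is not at fault here.

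**2. Precision.** With 35 + 35 analysed, one-sided power for 0.4 mg/dL is 97.2%. Removing 1, 3 or 5 CPP patients leaves 97.1%, 96.7% or 96.2%. Lost numbers are therefore not the issue.

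**3. Validity.** Let k be the number of CPP patients removed and D their mean creatinine minus the mean of those retained. The full-arm mean is [(35 − k) × retained mean + k × (retained mean + D)]/35 = retained mean + (k/35) × D. Removal therefore lowers the CPP mean by (k/35) × D. The protocol gives neither k nor D, so both are assumed:

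| k | D (mg/dL) | Shift (mg/dL) | Share of 0.4 |
|---|---|---|---|
| any | 0 | 0 | 0% |
| 1 | 1.0 | 1/35 × 1.0 = 0.03 | 7% |
| 3 | 1.0 | 3/35 × 1.0 = 0.09 | 21% |
| 5 | 1.0 | 5/35 × 1.0 = 0.14 | 36% |
| 5 | 2.0 | 5/35 × 2.0 = 0.29 | 71% |

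A negative D (removed patients healthier than those kept) reverses the sign. D = 2.0 is a severe case. It would arise, for example, if every removed patient took the 4 mg/dL that Outcomes {12} assigns to renal replacement therapy or death, and retained patients averaged 2.0.

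**4. False-positive rate.** This was simulated with no treatment effect, 40,000 runs, normal outcomes with SD 0.465, and k patients in each arm raised by D but removed from CPP only. The nominal one-sided 5% error in favour of CPP becomes about 7% (k = 1, D = 1.0), 15% (k = 3, D = 1.0), 26% (k = 5, D = 1.0) and 49% (k = 5, D = 2.0).

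**5. Shock criteria, sections side by side.** The Abstract and Participant timeline place allocation within 24 h of admission. The Concealment section settles eligibility before allocation. The Exclusion criteria use status at 24 h. All three can be met together only if allocation falls at hour 24. No section says that a patient already allocated is removed for shock at that point.

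**The case against.** The strongest reply is that the rule is narrower than it first looks. It covers only unforeseen delays that lack clinical justification. A catheter held back because the patient was unstable is the obvious justified case, and that patient stays in. A patient who dies within 24 h of allocation cannot build up a delay of more than 24 h. On its wording the rule is aimed at logistical failures, which may have little to do with prognosis. This stands. A reader might infer that the rule strips the sickest or early-dying patients from CPP and so makes it look better on creatinine, kidney injury and mortality. The text does not prescribe that; it would take misapplication of an undefined criterion by unblinded staff, which is possible but not given.

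There are also safeguards. Intervention initiation is to be reported, protocol modifications must be recorded, and an independent committee audits conduct after 20 and 40 patients. These make removals more visible but do not put the patients back. The 15% allowance covers numbers lost, not selective loss from one arm. Nor does section {20c} say that patients excluded under the timeline rule remain in the analysis; if their data collection stops, outcomes that are not imputed drop out anyway.

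On the shock criteria, a reader might infer a second post-randomisation exclusion that also breaks intention-to-treat. The article lists them as eligibility criteria and has eligibility checked before the envelope is opened. They would conflict with intention-to-treat only if applied to patients already allocated, and they would then apply to both arms.

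**Conclusion.** The contradiction is secure: the Participant timeline removes randomised patients under a rule that in practice only the CPP arm can trigger, section {20c} states intention-to-treat, and nothing else in the article resolves the two.

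Bias is a risk of unknown size and direction. Over the assumed values it runs from none (D = 0) to 0.29 mg/dL (k = 5, D = 2.0), with 0.03 to 0.14 mg/dL for D = 1.0 and k from 1 to 5. The documents do not support a claim that CPP will be favoured, because k and D are both assumptions and the rule's wording would normally keep unstable patients in.

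The shock criteria are a separate and lesser point: a timing inconsistency, not a stated removal after allocation.

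**What to change.** 1. Delete the exclusion sentence from the Participant timeline. State that every randomised patient is followed and analysed in the allocated arm.
2. Count late or absent catheter placement as non-adherence, which section {20c} already plans to report. If a per-protocol analysis is wanted, label it as sensitivity only.
3. Reconcile the Exclusion criteria with the Abstract, Participant timeline and Concealment mechanism, so that eligibility uses only information available before allocation and no allocated patient is removed under the shock criteria. Which time point is intended is for the investigators to settle. Moving it can change who is eligible, so this part is more than an edit of wording.

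**Cost.** Items 1 and 2 need a wording amendment and no extra patients. The downside is some dilution. If k CPP patients never received the catheter and gained nothing from allocation, a true 0.4 mg/dL would be estimated as 0.4 × (35 − k)/35: 0.37 for k = 3 and 0.34 for k = 5. Patients with a late catheter would dilute it less if they gained some benefit.

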### Sample size {14}

The sample size was calculated using the statistical noncentral *t *function, with a one-sided alpha level of 0.05 [31]. The calculations were based on the expected renal function and IAP variation between groups, since we assume the former to be dependent of the latter.

To support the trial rationale of an expected clinically significant IAP decrease of 3 mmHg in the intervention group, a total of 44 patients are considered necessary to detect a statistically significant difference, with 1:1 allocation ratio, 80% statistical power, and 95% confidence level. This estimate is based in a post-hoc analysis of 61 patients with cirrhosis from a multicentric randomized controlled trial in shock patients where a mean difference in IAP of 3 mmHg was found between survivors and non-survivors (13.7 ± 3.9 and 16.7 ± 3.9 mmHg, respectively) [4].

Regarding the primary outcome, to detect a clinically and statistically significant decrease in serum creatinine of 0,4 mg/dL in the intervention group, a total of 60 patients is estimated, with a 1:1 allocation ratio, 95% statistical power, and 95% confidence. This estimate is based on a multicentric observational study of acutely decompensated patients with cirrhosis. In this study, cirrhotic acute-on-chronic liver failure patients with at least one organ failure had a mean creatinine difference of 0,4 mg/dL between survivors and non-survivor groups (0.9 ± 0.45 and 1.3 ± 0.48 mg/dL) [32].

We arbitrarily estimate that protocol non-adherence/attrition or violation after randomization may affect approximately 15% of cases and, therefore, to ensure that the number of patients that complete the protocol is reached for the primary outcome, the total sample size is set at 70 patients with a 1:1 group allocation ratio.

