### Outcomes {12}

The primary outcome is serum creatinine concentration. The secondary outcomes are IAP, measured creatinine clearance, daily urine output, the multiorgan disfunction score Chronic Liver Failure Sequential Organ Failure Assessment (CLIF-SOFA) [13] and the incidence of stage 3 acute kidney injury (AKI) (defined by Kidney Disease: Improving Global Outcomes—KDIGO AKI [29] score), as well as 28-day renal replacement therapy (RRT)-free days, 28-day survival rate, and ICU LOS. The outcomes variables will be assessed at day seven (D7) after randomization (D0), unless otherwise stated. Additionally, IAP, serum creatinine concentration, measured creatinine clearance, daily urine output, and CLIF-SOFA will be analyzed using their maximum or minimum and daily mean values between D1 and D7.

Whenever ICU discharge or liver transplant occurs before D7, the last available data prior to these events will be used for outcome assessment. Additionally, stage 3 AKI will be considered when RRT or death occurs and, in these circumstances, a serum creatinine concentration value of 4 mg/dL and creatinine clearance value of 10 mL/min will be used for outcome assessment as mentioned in the literature [13, 29, 30].

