## Statistical methods

### Statistical methods for primary and secondary outcomes {20a}

For the descriptive analysis, quantitative variables will be reported as means and standard deviations or as medians and interquartile ranges (*P*_25_-*P*_75_), as appropriate, and categorical variables reported as frequencies and percentages.

Quantitative variables will be analyzed using the assessment day value (D7), the daily mean value, and their maximum or minimum values. Mann–Whitney *U* test will be used to compare study groups, assuming a non-normal distribution, or two independent sample *t*-test, in case of normal distribution. Dichotomous categorical variables will be analyzed using chi-square or Fisher’s exact tests. Using daily values, mixed effects regression models will be used to consider the autocorrelation structure between the longitudinal measurements. Regarding stage 3 AKI as secondary outcome, odds ratios and corresponding 95% confidence intervals will be estimated using logistic regression models. For the study of RRT-free days, competing risks survival models will be applied considering death as the competing risk. Regarding time until death, joint survival regression models will be used to take into consideration the association of longitudinal markers with time until death. For LOS, linear regression models will be applied. For all regression studies, univariable and multivariable analyses will be performed to account for potential confounders. The absolute risk of paracentesis-related complications will be reported for both trial groups. A level of significance *α*= 0.05 will be considered. Data will be analyzed using the R Statistical Software [41].

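### The 95% power is correct for measured creatinine, but the primary outcome scores death or RRT as 4 mg/dL, so that figure does not describe the outcome analysed

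*Protocol article*

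**What the plan says.** Sample size {14} uses the noncentral t function "with a one-sided alpha level of 0.05". The target is a "decrease in serum creatinine of 0,4 mg/dL in the intervention group", and the conclusion is that "a total of 60 patients is estimated, with a 1:1 allocation ratio, 95% statistical power, and 95% confidence". The inputs come from an observational study whose patients "had a mean creatinine difference of 0,4 mg/dL between survivors and non-survivor groups", with values of "0.9 ± 0.45 and 1.3 ± 0.48 mg/dL". The total is then raised to 70 for about 15% attrition or protocol violation.

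Outcomes {12} makes serum creatinine at day 7 the primary outcome. After RRT or death, "a serum creatinine concentration value of 4 mg/dL and creatinine clearance value of 10 mL/min will be used for outcome assessment". After earlier ICU discharge or transplant, the last available value is used.

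Statistical methods {20a} makes the test depend on distribution: the Mann-Whitney "test will be used to compare study groups, assuming a non-normal distribution, or two independent sample" t-test. On the level it says only: "A level of significance *α*= 0.05 will be considered".

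**The concern.** The variable that was sized is not the variable that will be analysed. Sample size {14} treats creatinine as roughly normal with an SD under 0.5 mg/dL. Outcomes {12} adds a cluster of patients at exactly 4 mg/dL. The sample size section neither mentions the substitution nor gives an expected share of patients affected. In the cited cohort the non-survivors averaged 1.3 mg/dL; in this trial any patient who dies by day 7 would score 4.

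The share cannot be taken as negligible. The population needs organ support, RRT at entry is not listed as an exclusion, and stage 3 AKI, RRT-free days and 28-day survival are all secondary outcomes.

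At stake is how a null result is read. With 95% power claimed, it would count as strong evidence against a 0.4 mg/dL effect, although the design may miss such an effect much more often than 1 time in 20.

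**Working it through.** **1. Reproduce the plan's figure.** Inputs from Sample size {14}: difference 0.4; SDs 0.45 and 0.48; one-sided alpha 0.05; 30 per arm.

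- Pooled SD = √[(0.45² + 0.48²)/2] = √0.21645 = 0.465.
- Noncentrality = 0.4 / (0.465 × √(2/30)) = 3.33, with 58 degrees of freedom.
- Power = 95.0%, so 60 patients reproduces exactly.
- With a two-sided test on the same inputs, power is 90.6% at 60 patients and 94.4% at 70; 74 patients (37 per arm) are needed for 95%.

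**2. Place the substituted value.** It lies (4 − 0.9)/0.45 = 6.9 SDs above one assumed mean and (4 − 1.3)/0.48 = 5.6 SDs above the other.

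**3. SD of the outcome as defined.** Let p be the share of patients set to 4, with the rest normal with mean m and SD s. Then variance = (1 − p)s² + p(1 − p)(4 − m)². With equal p in both arms and a 0.4 shift in measured values, the mean difference is 0.4(1 − p).

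Example, p = 10%:

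- Intervention: 0.9 × 0.2025 + 0.09 × 3.1² = 1.047.
- Control: 0.9 × 0.2304 + 0.09 × 2.7² = 0.863.
- Pooled SD = √[(1.047 + 0.863)/2] = 0.98. Mean difference = 0.36.

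**4. Power.** The protocol gives no value for p, so the range is an assumption. Power is simulated with 20,000 trials per row, and repeat runs differ by a point or two.

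| Share at 4 mg/dL, both arms | SD | t, one-sided, 30/arm | Mann-Whitney, one-sided, 30/arm | Mann-Whitney, one-sided, 35/arm | Mann-Whitney, two-sided, 30/arm |
|---|---|---|---|---|---|
| 0% | 0.47 | 95% | 94% | 96% | 88% |
| 2% | 0.62 | 79% | 92% | 95% | 86% |
| 5% | 0.78 | 60% | 89% | 92% | 81% |
| 10% | 0.98 | 42% | 81% | 86% | 71% |
| 20% | 1.24 | 26% | 63% | 69% | 50% |
| 30% | 1.39 | 19% | 45% | 50% | 33% |

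**5. Allow an effect on events as well** (0.4 shift in measured values, one-sided).

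- Events 20% in control, 10% in intervention: Mann-Whitney 91% at 30 per arm and 94% at 35; t-test about 70% at 30 per arm.
- Events 30% and 20%: Mann-Whitney 79% at 30 per arm and 84% at 35; t-test about 53% at 30 per arm.
- If a 0.4 mg/dL mean difference arises only from fewer events, with measured values alike, Mann-Whitney power is about 24% and t-test power 28 to 43% at 30 per arm (control event share 20 to 50%).

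**6. Order of scores.** Entry creatinine has no upper limit, and the upper stratum is open-ended at 1.5 mg/dL or more. A survivor off RRT at 4.5 mg/dL therefore ranks worse than a patient who died and was scored 4.

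**The case against.** Several parts of the opposing case stand.

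- **Arithmetic.** A reader might infer a calculation error. There is none: 60 patients follows from the stated inputs. The fault is a mismatch between the sizing and the outcome definition.
- **Sidedness.** A reader might infer that the analysis section contradicts the one-sided sizing. It does not: the one-sided level is stated openly, and Statistical methods {20a} gives no sidedness. The 95% confidence intervals named there are for stage 3 AKI odds ratios, so they do not settle the primary test. What remains is an ambiguity worth about four points of power at 60 patients.
- **Size of the loss.** A reader might infer that power is far lower whatever happens, or that the SD is two to three times larger as a matter of fact. Both depend on the assumed share: the SD ratio is about 1.3 at 2%, 1.7 at 5%, and reaches two to three only at about 10 to 30%. The steep t-test losses are also unlikely to apply, because a cluster at 4 makes the data non-normal and the plan then points to Mann-Whitney.
- **Patients available.** Analysis is by intention to treat and deaths and RRT receive a value, so those events do not reduce the sample. Up to 70 patients may contribute.
- **Effect on events.** The trial hypothesis expects better outcomes, and fewer events under the intervention would recover much of the power.

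These points narrow the size of the problem. They do not make the 95% a property of the outcome analysed, because it depends on an event share and an effect on events that the protocol never states.

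**Conclusion.** The point holds as a mismatch. The stated 95% applies to measured creatinine under a one-sided t-test and not to the primary outcome as defined. Under the preferred rank test, with no effect on events, the loss is small at a 2% share, moderate at 10% and large from about 20%. At 30 per arm none of the scenarios examined with a share above zero reaches 95%; with all 70 patients only the 2% share comes to about that level.

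This rests on assumed event shares, normal measured values with the protocol's means and SDs, and a 0.4 mg/dL shift in patients without an event. The trial stratifies at 1.5 mg/dL, so measured values may vary more than the cited SDs suggest; the table makes no allowance for that.

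That 4 mg/dL is not a worst value is a separate, secondary point. How often a survivor off RRT exceeds 4 is unknown from the protocol, so it supports a sensitivity analysis and not a replacement of the primary scoring.

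**What to change.** 1. In Sample size {14}, withdraw the unconditional 95%. Restate power by simulation for the outcome as defined in Outcomes {12}, over a stated range of death/RRT shares, with and without an effect on events, at 60 and 70 patients.
2. In Statistical methods {20a}, name the Mann-Whitney test as the single primary test. At a 10% share the choice between the two tests moves one-sided power from 42% to 81%, so it should not hang on a normality check.
3. State the same sidedness in both sections. If two-sided is chosen, the protocol's existing inputs give 91% at 60 patients and 94% at 70, before the 4 mg/dL rule is considered.
4. Keep 4 mg/dL in the primary analysis and add a sensitivity analysis that ranks death and RRT above any observed creatinine. Re-ranking the primary outcome itself would be an endpoint change in a recruiting, open-label trial with unblinded analysts, and is not needed here.

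The cost is one simulation and a dated amendment, preferably made before any comparison by arm, including the interim look planned at 30 patients. No patients are added. The drawback is that the stated power becomes less favourable.
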